## Abstract

**Background:**

Although many mHealth interventions have shown efficacy in research, few have been effectively implemented and sustained in real-world health system settings. Despite this programmatic gap, there is limited conclusive evidence identifying the factors that affect the implementation and successful integration of mHealth into a health system.

**Objective:**

The aim of this study is to examine the individual, organizational, and external level factors associated with the effective implementation of WelTel, an mHealth intervention designed to support outpatient medication adherence and engagement in care in Africa and North America.

**Methods:**

We will adopt the Consolidated Framework for Implementation Research (CFIR) constructs for evaluation of mHealth implementation including a scoring and monitoring system. We will apply the adapted tool to identify facilitators and barriers to implementation of the WelTel mHealth intervention in order to determine how the technology platform is perceived, diffused, adapted, and used by different mHealth project teams and health system actors in Africa and North America. We will use a mixed-methods approach to quantitatively test whether the factors identified in the CFIR framework are associated with the successful uptake of the mHealth intervention toward implementation goals. We will triangulate these data through interviews and focus group discussion with project stakeholders, exploring factors associated with successful implementation and sustainment of these interventions.

**Results:**

The development of the customized CFIR is finalized and currently is in pilot testing. The initial results of the use of the tool in those 13 implementations will be available in 2019. Continuous conference and peer- reviewed publications will be published in the coming years.

**Conclusions:**

The results of this study will provide an in-depth understanding of individual, organizational, and external level factors that influence the successful implementation of mHealth in different health systems and geographic contexts over time. Via the tool’s unique scoring system connected to qualitative descriptors, these data will inform the most critical implementation targets and contribute to the tailoring of strategies that will assist the health system in overcoming barriers to implementation, and ultimately, improve treatment adherence and engagement in care.

**Registered Report Identifier:**

RR1-10.2196/9633

## Introduction

### Background

Billions of dollars are globally spent on health research projects each year, but only a limited number of effective interventions are translated into practice and policy [1,2]. Technology is providing unprecedented opportunities to improve patient engagement in care for better adherence leading to reduced morbidity and mortality, yet a significant knowledge-action gap remains [2]. Many evidence-based innovations are not adequately scaled up to meet the full challenges of the United Nations’ global Sustainable Development Goals [1,3-5]. Mobile health (mHealth) is an emerging area of disease management that can help patients adhere to prolonged treatment regimens and improve their quality of care—an area where improvement can have more impact than even discovery of new treatments. Globally, mobile phones are now the most pervasive and accessible form of two-way communication technology. In 2014, the number of mobile phone subscriptions surpassed the number of people, and uptake in vulnerable and marginalized groups has, in many cases, bridged the socioeconomic “digital divide” [6]. Text messaging via short message service (SMS) remains one of the most popular forms of mobile communication and has become the most used data transfer system in the world, with over 24 billion text messages sent and received each day. A landmark randomized controlled trial (RCT), WelTel Kenya1, was the first comprehensive RCT to test effects of text message reminders in improving HIV therapy adherence. The authors showed that bi-directional, weekly text messaging significantly improved adherence to antiretroviral therapy (ART) and increased the proportion of patients with a suppressed HIV viral load in an HIV-positive Kenyan population initiating ART, over a 1-year period [7]. As noted by a recent Cochrane review, this RCT study (and many others) have built a strong body of high-quality evidence supporting the use of weekly text messaging to enhance ART adherence and viral suppression, in comparison to current standards of HIV/AIDS care [8].

Since the original RCT, the WelTel mHealth program has expanded in Africa and North America in the area of HIV/AIDS [9-12], tuberculosis (TB) [13], maternal and child care, asthma, and recently in primary care settings. The WelTel program is a patient-centered form of digital outreach communications designed to support engagement in care and treatment adherence. Using a weekly check-in model, usually via text message, patients self-identify concerns that are then triaged by a point person and connected for care to appropriate health care providers on an “as-needs” basis, leading to a form of patient-centered precision care. With its leading evidence base in HIV and TB, the WelTel program is ideal for an implementation science evaluation as it is in the process of being scaled-up in numerous settings.

Case studies, RCTs, and other quasi-experimental methods generate critically important evidence to determine the efficacy of an intervention. These methods, however, do not provide the necessary information required to implement comprehensive public health interventions in real-life settings. Implementation science can help fill this gap by studying the process of developing, introducing, institutionalizing, and sustaining policies, programs, and activities in complex settings. This is done by identifying the individual, population, health system, and health environment factors associated with the successful uptake of effective interventions [5,14-18].

Undertaking a comprehensive implementation science study is particularly important when studying mHealth interventions, as the health care system itself is complex, includes multiple interacting components, and interventions must be adapted to fit the needs of a practice setting and patients with different views and expectations [19,20]. However, to our knowledge there is no tested tool that can be continuously used to evaluate, monitor, and inform mHealth implementation processes as they unfold.

### Aim

The overarching aim of our 5-year research project is to create and test an implementation research tool that can be used to generate continuous, context-specific evidence that can inform mHealth for impact at scale. To do so, we will evaluate the scale-up process of the WelTel text-messaging mHealth system in different global implementation settings. We will use rigorous scientific methods to assess processes and outcomes with the following main objectives:

To adapt the Consolidated Framework for Implementation Research (CFIR) constructs for evaluation of mHealth implementation including a scoring and monitoring systemTo apply the adapted tool to identify facilitators and barriers to implementation within each program to continuously inform the implementation processTo use a scoring framework to correlate implementation factors with measures of implementation success (rate and scale of adoption plus sustainability) across the multiple projects over time

### Conceptual Framework

This comprehensive mHealth implementation science study will use the widely cited and used CFIR [5]. The CFIR is an implementation science framework that provides a comprehensive taxonomy of operationally defined constructs from multiple disciplinary domains (eg, psychology, sociology, organizational change) that are likely to influence implementation of complex programs. CFIR constructs are organized into five major domains: (1) characteristics of the intervention (eg, evidence strength and quality, complexity), (2) the outer setting (eg, patient needs and resources), (3) inner setting (eg, compatibility of the mHealth intervention with existing engagement programs, leadership engagement), (4) characteristics of individuals involved (eg, knowledge and attitudes), and (5) the process used to implement the program (eg, quality and extent of planning, engagement of key stakeholders) [5]. We are using this framework with the primary aim of understanding how the WelTel mHealth program is perceived, diffused, adapted, and used by different mHealth project teams and health system actors in Africa and North America. The CFIR framework draws together the unique and common elements of 19 different theories and frameworks and offers a common taxonomy for exploring the effectiveness of implementation within a specific context [5]. While theoretical frameworks in implementation studies are underused [21], the use of theory in implementation studies can help identify factors that predict the likelihood of implementation success and help develop better strategies to achieve more successful implementation, thus strengthening the understanding and explanation of how and why implementation succeeds or fails (eg, what works, for whom, under what circumstances, and why) [22]. Theories, frameworks, and models can help identify appropriate outcomes, measures, and variables of interest for implementation studies. Theory can also help organize studies when collecting, analyzing, interpreting, explaining, and presenting data [23].

In preparation for this study, the appropriateness of several theories and frameworks were assessed. Several implementation frameworks and theories that exist were considered relevant, such as the Reach Effectiveness Adoption Implementation Maintenance framework [24], the Promoting Action on Research Implementation in Health Services framework [25], the Technology Acceptance Model [21], and the Normalization Process Theory [22]. The CFIR was chosen based on its comprehensiveness and ability to manage both breadth and depth of data given the complexity of mHealth programs. It includes a broad number of aspects related to implementation and is thus considered a helpful framework for identifying barriers and facilitators influencing mHealth implementation. It addresses the need to assess and maximize the effectiveness of implementation within a specific context and to promote dissemination to other contexts.

Since its inception, CFIR has largely been used to help understand the interplay between context and the implementation process. This framework can therefore be adapted and used to guide the design of mHealth interventions for particular settings, as well as the study of their implementation. An increasing number of implementation studies have used CFIR, some as an evaluation framework [23,26,27], some for detecting factors influencing implementation [28,29], and some for classifying these influencing factors as facilitators or barriers [19,26]. To date, only a few studies have employed the CFIR for evaluation of specific technological interventions [19,30,31]. We found only two other studies that used the CFIR developers’ method to identify and compare distinguishing constructs between high versus low implementation settings [19,32]. We were unable to find any studies that compared implementation factors in high- and low-resource settings. Finally, we did not find any studies that considered the dynamic nature of implementation by examining barriers and facilitators over time. [33-36]. There is a need for research that assesses, tests, and further develops CFIR’s applicability in determining which factors influence implementation success in the field of mHealth interventions. We will tailor the CFIR for use with mHealth interventions in different settings and contexts.

### Intervention Details

The WelTel innovation is an evidence-based, low-cost, easy-to-use, and accessible mobile phone‒based health communication solution to address the global challenge of inadequate outpatient engagement across multiple diseases. Developed with direct input from patients and caregivers in Kenya, the original WelTel model for HIV care was a weekly two-way text-message check-in by clinic staff to patients using basic mobile phones. Clinicians called patients if they reported a problem via text message, triaged those problems, and provided advice on how to manage them (eg, a care path). This method was first validated in the landmark RCT, WelTel Kenya1, which demonstrated improved patient adherence to HIV treatments and achieving viral suppression, a key target of the World Health Organization (WHO) and the Joint United Nations Programme on HIV and AIDS (UNAIDS) 90-90-90 target [7]. The mobile communication model was intended to provide patients with extra support between clinic visits, while maintaining maximal reach and privacy protection through its simplicity and lack of outgoing health-related content. It also extends the capacity of health care providers to look after patients by proactively managing outpatient problems and identifying individuals who require the most support (only 3% of patients identified “problems” each week). Multiple studies have since validated elements of the intervention, such as preferred message frequency (weekly better than daily) and the two-way nature of communication (versus one-way) [37]. The WelTel innovation, and evidence surrounding it, has directly informed global treatment guidelines such as the 2013 WHO ART guidelines and the 2014 International Association of Providers of AIDS Care guidelines for retention in HIV care. Regardless of its effectiveness, there are also different user and technological level challenges in different contexts. The WelTel service has been adapted for TB; maternal, neonatal, and child health; and asthma programs, with interest and the potential to expand to other health conditions in the future (eg, cancer care, primary care). In our adoption of WelTel for TB in British Columbia, Canada, we found that WelTel weekly two-way text messaging did not improve latent TB infection (LTBI) completion rates compared to standard LTBI care. However, completion rates were high in both treatment arms [38]. In a recent RCT to determine whether a text-messaging intervention improved retention during the first year of HIV care, WelTel’s weekly text-messaging service did not improve retention of people in early HIV care [39]. With all this mixed evidence and effectiveness across different implementations, we are proposing a continuous 5-year implementation science research on this intervention to identify what works and what does not.

## Methods

### Overview

In this cross-project, mixed-methods study, we will take an investigative approach to determining what works, what does not, and the specific barriers and facilitators to implementing the WelTel mHealth service at various programmatic stages. Using a standardized adapted CFIR tool, 13 initial projects will be evaluated at their current state and followed over time at 6-month intervals for up to 5 years. In addition to the adapted CFIR domain narratives, each domain will be scored using a standardized scoring technique (see below) and compared both across projects and longitudinally within projects. The scoring will be used to identify domains and elements within the domains that appear to be doing well (scored highly) or doing poorly (low scores), and how they are associated with successful progress in the implementation of the projects. These factors will then be discriminated in a way that can actively inform individual projects along the implementation process and ultimately lead to an optimized and cost-effective mHealth strengthening opportunity for these health services globally. The evidence from data collection every 6 months will be iteratively analyzed and used as an input to inform the implementation process. The results of each project will be shared with the respective project leaders and discussed in the bi-annual meetings of the research team on the modality of incorporating the evidence into the implementation process. Continuous support will be provided by the research team to see the level of incorporation of the research results into the implementation. Experience sharing visits will be also organized among different projects to facilitate evidence use among all 13 projects.

A novel feature of this study will be a cross-project implementation science evaluation using the CFIR framework. An international consortium for implementation science recognized the need to not only evaluate study endpoints but also conduct formative evaluations to assess the extent to which implementation is effective in a specific context to optimize an intervention’s benefits, improve sustainability, and promote dissemination of findings into other settings. The framework not only evaluates static components of implementation factors that facilitate or impede implementation success but also evaluates processes over time. The CFIR framework is flexible and was designed to be adaptable to a program’s specific needs. For our purposes, we will create a standardized scoring framework and narrative based on the most salient individual constructs of the framework for mHealth research and our specific intervention. This allows us to compare implementation factors across our individual studies in a standardized way and also evaluate them dynamically over time [40].

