### Data Collection

Members of the mHealth research team will conduct one-on-one interviews or focus groups (depending on availability and preference of participants) using a purposive sampling strategy that focuses on individuals who are involved in the planning, implementation, or follow-up of their respective mHealth studies. Participants will consist of individual project relevant/representative stakeholders representing the range of stakeholders and representing the five domains. Five people from each project will be included in the qualitative study. To avoid bias, participants will be selected by each project leader rather than the central WelTel team. They will be asked to provide written informed consent. Interviews will be conducted at locations that are convenient for the key stakeholders and will ensure their privacy and confidentiality. Participants will have the opportunity to discuss potential strategies about how their respective project(s) could be improved or strengthened, the influence of internal and external social relationships and climate on the study and acceptance of the intervention, and suggestions for the WelTel mHealth intervention itself. Engaging with these team members through interviews or small focus groups will provide important insights that can guide implementation of the WelTel mHealth intervention in specific contexts. As each project team is at a different phase of their project, we will investigate difference stages of project development, implementation, and follow-up. Data will be collected every 6 months from each of the projects for 5 years.

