### Scoring

Each of the constructs in the modified CFIR will have scoring out of 10. Each of the participants will score each of the constructs, and the median will be automatically calculated. A 10-point scoring approach will be used to flexibly capture the opinion of the study participants. A unique scoring guide will be used to maintain consistency among individual assessments and for standardized comparison across studies and over time. Figure 1, adapted from the original CFIR authors [5], shows the scoring system that will be used to score each of the CFIR constructs based on the level of influence they have on the implementation outcome.

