### Participants

The main participants of this study will be stakeholders, individual project team members, and patients of the different implementations in global settings. Project team members who worked for more than 6 months will be eligible to be study participants to make sure they received enough exposure and experience about the project. For project participants, those who are older than 18 years of old will be included. As per our knowledge, most of the projects have an average of 5 team members to run the intervention. Hence, we target 5 participants for each stage of the assessment per project until saturation is reached.

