## Discussion

### Principal Considerations

While there are many pilot studies and trials investigating the application of mHealth to improve adherence and other health outcome indicators, such as morbidity and mortality, there is a lack of sufficient evidence to inform the scale-up of mHealth programs in real-world settings. According to Luoto et al [41], ideal evidence for scale-up of mHealth programs includes efficacy (does it work?), effectiveness (does it work in a variety of populations and contexts?), and sustainability (cost effectiveness, demand, adaptation into health system). Following on from this, the overarching goal of our proposed research is, therefore, to close the gap in the evidence required to deliver an effective mHealth service to support patient care at scale in multiple global settings.

Our proposed implementation science study contains four important innovations. First, this study comprises 13 currently funded mHealth projects and programs. As outlined by Edwards et al [42], without attending to context and how it interacts with interventions, implementation of interventions are likely to fail or underperform. Hence our study, based in four countries across two continents, will provide robust, context-specific implementation science evidence to assist in moving the mHealth field forward.

Second, this proposed implementation science study will also compare barriers and facilitators to implementation of mHealth in both high-resource and low-resource settings. Sood et al [43] conducted a systematic review to compare different facilitators and barriers in developed and developing countries for successful electronic medical record implementation and use and found a major difference in barriers in those two settings. However, with respect to the implementation of mHealth interventions, this type of analysis is lacking and this study aims to fill this evidence gap. The results of this study therefore might advance the field of mHealth implementation science by examining predictors of implementation and sustainability as a function of intervention stage, which will give us implementation status‒based evidence to inform future implementation of similar interventions.

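### Scores from raters likely to know their project's progress are fed back to all 13 projects and then tested as predictors of success, with no time order fixed and feedback not named as a limitation

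*Protocol article*

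**What the plan says.** **Schedule.** Under Overview, "13 initial projects will be evaluated at their current state and followed over time at 6-month intervals for up to 5 years". Data Collection repeats the 6-month interval: "Data will be collected every 6 months from each of the projects for 5 years".

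**Who scores, and what.** Under Scoring, "Each of the participants will score each of the constructs, and the median will be automatically calculated". That section also says that a construct is rated by how much it influences the implementation outcome, while Overview reads a high score as a domain that is going well. Under Participants, "Project team members who worked for more than 6 months will be eligible to be study participants"; stakeholders and patients are listed too, with a target of five participants per project. Data Collection adds that "participants will be selected by each project leader rather than the central WelTel team".

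**What happens to the scores.** Overview: "The evidence from data collection every 6 months will be iteratively analyzed and used as an input to inform the implementation process". Each project's results go to its leader, the research team follows up with continuing support, and "Experience sharing visits will be also organized among different projects to facilitate evidence use among all 13 projects". No project is described as going without feedback.

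**What the scores are tested against.** The third objective under Aim correlates the factors with implementation success, meaning rate and scale of adoption plus sustainability. Analysis names t tests, clustering or repeated-measures methods, the choice depending on the data.

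**What is claimed.** Principal Considerations speaks of "examining predictors of implementation and sustainability as a function of intervention stage". The term predictors appears again later in that section and under Strengths and Limitations. The limitations admit that scores rest on perception and offer five raters per project as the remedy. Feedback and visits between projects are not mentioned there.

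**The concern.** One set of scores does two jobs. It is the explanatory variable in the test against success, and it triggers action that is meant to change success. Two distortions follow, and they can pull in opposite directions.

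- **Rater reaction.** A team member of more than six months' standing can be expected to know whether the project is going well. If that knowledge colours the ratings, progress produces the score and not the reverse. Five raters who share the knowledge share the bias, and their median keeps it.
- **Feedback.** If a low score brings help, progress improves after low scores. A real barrier can then look unimportant, or even appear with the wrong sign. Visits between projects also mean that the 13 units influence one another.

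The aim is to tell other programmes which factors to work on. Reporting a consequence of success as its predictor, or missing a barrier because feedback corrected it, would misdirect them.

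**Working it through.** **Stated figures.** The article gives no alpha, power, effect size or SD for the association between score and success, so there is no planned figure to reproduce. What follows is an illustration.

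**Inputs from the protocol**
- 13 projects (Overview).
- 5 years × 2 rounds a year = 10 follow-up rounds, or 11 with the entry assessment.
- 5 raters per project, summarised by the median (Participants; Scoring).

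**Assumed inputs, on an SD-like scale**
- Factor effect on next-round progress, β: 0 or 0.3.
- Rater reaction to current progress, r: 0 to 1.
- Corrective feedback, f: 0 or 0.3.
- A complete panel of 13 projects. The protocol allows projects to be added, removed or replaced, so this is a simplification.

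**Model**, with F the true factor, u a project effect, y progress and s the score:
- s(t) = median over 5 raters of [F(t) + r·y(t) + N(0,1)]
- y(t) = 0.6·y(t−1) + 0.4·u + β·F(t−1) − f·s(t−1) + noise of SD 0.6

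The term −f·s makes a low score lead to better progress in the next round.

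**Analyses**, two-sided 5%, 4,000 runs each:
- A: correlation of project-mean score with project-mean progress.
- B: t test of last-round scores, the six most against the six least successful projects.
- C: progress at the second assessment regressed on score and progress at the first.

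| β | r | f | A rejects | B rejects | C rejects | C mean slope |
|---|---|---|---|---|---|---|
| 0 | 0 | 0 | 4.5% | 4.8% | 5.0% | −0.001 |
| 0 | 0.25 | 0 | 12.2% | 8.1% | 4.5% | −0.001 |
| 0 | 0.5 | 0 | 33.9% | 17.8% | 5.0% | −0.002 |
| 0 | 1.0 | 0 | 81.6% | 46.9% | 5.4% | 0.000 |
| 0.3 | 0 | 0 | 48.8% | 11.7% | 16.5% | 0.197 |
| 0.3 | 0 | 0.3 | 5.0% | 4.4% | 8.3% | −0.105 |
| 0.3 | 0.5 | 0.3 | 26.6% | 14.9% | 8.0% | −0.098 |
| 0 | 0.5 | 0.3 | 6.2% | 7.0% | 36.3% | −0.304 |

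**Reading the table**
1. *Rater reaction alone (rows 1 to 4).* Same-time analyses find associations that are not causes, despite the median of five. The lagged, adjusted analysis stays at 4.5% to 5.4%. Simulation error around 5% is ±1.96·√(0.05·0.95/4000) = ±0.7 points, so this is nominal.
2. *Feedback hiding a real factor (rows 5 and 6).* Rejections by A fall from 48.8% to 5.0%.
3. *Feedback and the lagged slope.* The slope moves by about −f: 0.197 − 0.3 = −0.103 (simulated −0.105), and 0 − 0.3 = −0.3 (simulated −0.304). A true positive effect changes sign, and a null factor is rejected in 36.3% of runs. Lagging does not remove the feedback effect.

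**The case against.** **Timing is a model detail.** The objective speaks of correlation over time, Overview plans comparison within projects, and repeated-measures analysis is among the options. A reader might infer that scores will be set against success in the same round. The article does not say so, and a full analysis plan could set a lag. This stands: same-time analysis is one permitted route, not the stated one.

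**The design does not prevent separation.** A reader might also infer that prediction and rater reaction can never be told apart here. That goes too far. The 6-monthly data allow a score to be related to later progress, with adjustment for recorded progress, and in the simulation without feedback this kept false positives at their nominal rate. The difficulty is harder for feedback, because every project receives it.

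**Feedback is intended.** The second objective is to inform implementation continuously, so feeding results back is no error. The operative sections mostly speak of association; predictors is Discussion language, partly hedged. This stands too, but the Discussion is where readers will take the conclusion from, and its limitations are silent on feedback.

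**The figures are built on assumptions.** They are. No passage gives r, f or β, and Figure 1, which shows the scoring scale, is not visible. The numbers show direction and possibility, not the expected error in this study.

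An unseen analysis plan does not settle everything. A dated record of what was fed back and acted on is data collection, and it is hard to rebuild afterwards.

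**Conclusion.** The point holds in this form. Raters likely to know their project's progress produce scores that are fed back in all 13 projects, and the same scores are tested against success and described as predictors. No time order is fixed and feedback is not acknowledged as a limitation. An association may be a reaction to known progress, and corrective feedback may mask or reverse a real one.

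The size cannot be taken from the documents. Under the assumptions above, false positives in a same-time correlation run from 4.5% with no rater reaction to 82% at a reaction of 1.0, and from 5% to 47% for the t test. Feedback of 0.3 removes the power to see a factor effect of 0.3 and turns its lagged slope from about +0.20 to about −0.10.

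The documents do not support saying that the analysis is concurrent, that the predictors are necessarily spurious, or that the feedback should stop. Nor would a lagged model alone cure the problem. The change is worth making because it limits what may be concluded, and it is cheap.

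**What to change.** 1. Keep the formative feedback.
2. Collect each round's scores before that round's results are shown to the project.
3. Keep a dated log per project of feedback acted on, support contacts and sharing visits.
4. Alongside the planned analyses, relate the score at round t to progress from t to t+1, adjusted for progress at t, with logged feedback as a covariate. State that the lag deals with reaction to recorded progress but does not by itself remove the feedback effect. The log helps only so far as action differs between projects with similar scores.
5. Report the first-round score against later progress, adjusted for progress at entry, as a sensitivity analysis. That score precedes any feedback, though the progress that follows does not. The adjustment is needed because Principal Considerations says that some projects are already adopted as regular programmes.
6. Call same-round associations correlates, and name feedback and visits between projects under Strengths and Limitations.

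**Cost.** Wording, one added analysis and a simple log of activities already planned. The last round has no following outcome, so it drops out as an explanatory round in the lagged analysis.
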